### Statistical analysis

Sample size and power calculations are based on comparing expected change in medication adherence rate of patients in each group at six months - an expected adherence mean difference of 10 % based on our pilot study findings and the literature. We use an alpha of .05 and provide for 90 % power to detect indicated effect sizes in this two-arm randomized study. An effect size difference of 70 % is based on a conservative estimate of our pilot work. A sample size of 46 older KT recipients per group (final total sample 92) will meet these assumptions and provide sufficient power. Recruitment and retention rates are calculated from our pilot study, other adherence studies at the same sites, and are documented in one similar RCT adherence study in older KT recipients [63, 64]. We selected an adherence rate of 85 % to divide the adherers from the non-adherers based upon our preliminary work describing 4 clusters of KT medication adherers: those who (1) take medications on time (1.0-.85 MA rate), (2) take medications on time with late/missed doses (.84-.70 MA rate), (3) rarely take medications on time and who were late with morning and/or evening doses (.69-.20 MA rate), and (4) missed many doses (<.20). Even minor deviations in dosing adherence lead to poor outcomes, though no studies have determined the criterion adherence “dose” that distinguishes good and poor outcomes.

Appropriate descriptive analyses will be performed to examine distributional characteristics for collected measures, as well as to summarize changes over time as a function of group assignment. During this initial phase, we will explore bivariate relationships among primary and secondary outcome measures and variables thought to affect medication adherence. In addition, we will conduct analyses to determine whether the randomly assigned groups are equivalent at the start of the study on the demographic and other measures collected at baseline. Before hypothesis-testing analyses are conducted, exploratory analyses will be performed to examine the effect of various mediators and moderators on the relationship between intervention, adherence, and clinical outcome. The results of these analyses will determine what additional variables will be incorporated in the subsequent hypothesis testing (e.g., analysis of covariance).

Our primary analysis assesses whether the SystemCHANGE™ intervention is more effective than the attention-control intervention in increasing MA in adult kidney transplant recipients at the completion of the 6-month intervention and 6-month maintenance phases. We hypothesize that adult kidney transplant recipients receiving the SystemCHANGE™ intervention will have higher immunosuppressive MA rates than the attention-control group at the completion of intervention and maintenance phases. Since rate responses will most likely violate the normality assumption, the non-parametric method, Mann- Whitney test, will be used for comparing the two groups. However if the normal assumption is satisfied through transformation or as raw data measures, t-test will be applied for group comparison. Possible covariates resulting from demographic data and screening phase MA will be included in the analysis to adjust for possible bias.

Our secondary analysis assesses the MA patterns in both the SystemCHANGE™ and attention-control groups. Specifically we are interested in determining when the intervention becomes effective (e.g., what “dose” is needed) and the pattern of decay in MA over time in both groups. The dependent variable for these research questions are the repeated measurements of immunosuppressive MA rates at 12 time points [i.e. 1, 2, 3, 4, 5, 6, 7, 8, 9, 10, 11 and 12 months] and the independent variable is group assignment and time effect. Poisson regression analysis will be used for these questions. Proc Nlmixed procedure in SAS will be used for Poisson regression modeling. In order to answer the hypothesis we will test for group-by-time interaction to test if the two groups have different time profiles for MA or not. Possible covariates resulting from demographic data and screening phase MA will be included in the model to adjust for possible bias. Repeated measures from the same Pp will be accounted for using a random effect in the model.

Our exploratory analyses focuses on three aims: 1) to determine whether the SystemCHANGE™ intervention is more effective than the attention-control intervention in decreasing poor health outcomes (e.g. increasing creatinine/BUN, infection, acute/chronic rejection, graft loss, death), 2) to evaluate the role of potential mediators (social support, and systems-thinking) and moderators (ethnicity perceived health and level of medication nonadherence) of MA and health outcomes in adult kidney transplant recipients receiving the SystemCHANGE™ intervention, and 3) to determine if the SystemCHANGE™ intervention is cost-effective.

We expect to observe lower levels of poor health outcomes in the SystemCHANGE™ group as compared to the control group. The dependent variables are the dichotomous outcomes such as, infection, acute and chronic rejection, graft loss, and death and numeric outcomes such as creatinine, and BUN.

The independent variable is group assignment. Chi-square tests will be applied to estimate and test the relationships between dichotomous outcome variables and the independent variable. For continuous outcomes variables t test or Mann-Whitney test will be conducted to test for group effect depending on the satisfaction of normality assumption.

Our secondary exploratory aim is to evaluate the role of potential mediators and moderators of MA and health outcomes in adult kidney transplant recipients receiving the SystemCHANGE™ intervention and recipients receiving the attention-control intervention. We hypothesize that exploring potential mediators and moderators in the analyses will enhance the interpretation of treatment effect on MA. To test for mediator effect, the dependent variable is MA and the independent variable is treatment group. Potential mediators are social support and systems thinking. Poisson regression will be applied to estimate the mediator effect [65] and the Sobel test [66] will be used to test if the mediator effect is significant. Changes in the variance with mediator in the models will be estimated and reported as part of the analysis results. To test for moderator effect, the dependent variable is MA and the independent variable is treatment group. Potential mediators are ethnicity group, perceived health and MA level (different strata). Poisson regression will be applied to estimate and test for possible moderator effect through interaction terms between the independent variable and moderator [65].

Our third exploratory aim is to determine if the SystemCHANGE™ intervention is cost-effective. Our hypothesis is the cost for the SystemCHANGE™ intervention will be less than the cost for the attention-control intervention. To determine the cost-effectiveness of the SystemCHANGE™ intervention compared to the attention-control intervention, both intervention and resource use costs will be evaluated and compared to MA change. A cost-effectiveness analysis will be performed at the end of the intervention period and again at the end of the maintenance period. If there is no treatment effect, a cost-analysis will not be performed. The analysis performed at the end of the maintenance period will be cumulative, incorporating costs and benefits incurred throughout the project. A cost-effectiveness analysis, performed at the end of the maintenance period (calculated for both the intervention and maintenance periods), will evaluate both intervention and control, and resource use costs which will be compared to adherence change. The sum of the total intervention and control costs and resource use costs will be the numerators for testing this hypothesis. The change in adherence (from baseline to end of intervention [or end of maintenance] period) will be the denominator. We will identify all direct intervention costs related to the intervention and the control (planning, designing, and implementation of each intervention, personnel, supplies, travel, and equipment). We will identify resource use costs (hospitalizations, clinic, observation, and ER visits) for both groups. Resource use costs will be obtained from publically available data, e.g. Hospital Compare, Hospital Stats, H-CUP. The DRG will be obtained with a conversion rate and then adjusted by hospital specific information, e.g. academic, location.

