### Primary outcome - medication adherence

Table 2 provides an overview of study measures and outcomes. The MA calculation method has been previously described but will be briefly described here [41]. A 0.5 is assigned if the dose of the immunosuppressive medication is taken within a 3-hour window (+/-1.5 hours of the prescribed time); 0.25 is assigned if the dose of the immunosuppressive medication is not within the 3-hour window but is taken within a 12-hour window (+/-6 hours of the prescribed time), and 0 is assigned if the dose of the immunosuppressive medication is not taken within a 12-hour window (+/-6 hours of the prescribed time, i.e., if the dose was missed). On each day, an individual is assigned a score of 0, 0.25, 0.50, 0.75 or 1 points (p. 526).

**Table 2 Tab2:** Study outcomes and measures

	Screening	Intervention	Maintenance
*Inclusion Criteria*			
6-item telephone measure of cognition	√		
Primary Outcome			
Medication adherence–electronic medication monitoring	√	√	√
Secondary Outcomes			
Creatinine	√	√	√
Blood urea nitrogen	√	√	√
Acute rejection	√	√	√
Chronic rejection	√	√	√
Infection	√	√	√
Death	√	√	√
*Potential Mediators*			
Social Support		√	√
Perceived Health		√	√
Personal Systems Thinking		√	√
*Background*/*Moderating Variables*			
Medical History	√		
Demographics (ethnicity)	√		
Level of Medication Nonadherence	√		
Pillbox use	√		
*Health care costs*			
Hospitalizations, clinic, observation, and ER visits	√	√	√

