### Potential moderators and mediators

Perceived health status, a potential moderator, will be measured by one question, “In general, how would you say your health is?” Respondents select excellent, very good, good, fair, or poor. Perceived health status reflects people’s overall perception of their health, including both physical and psychological dimensions [58]. The question has good reliability and validity [58]. Ethnicity will also be examined as a moderator.

Potential mediators are examined including social support and systems-thinking. We measure social support using the Social Support Appraisals Index, a 23-item self-administered, self-report scale measuring the degree to which a person feels cared for, respected, and involved with family and friends [59]. Respondents strongly agree, agree, disagree, or strongly disagree with each statement. Total scores range from 23 to 92. After reversing the negatively stated items, low scores indicate high levels of support. Typically, subscale scores for family and friends are calculated. The instrument has been used with adult kidney transplant recipients [43, 60]. Data from 10 samples indicate that the scale had good internal reliability, with Cronbach’s alphas ranging from .80 to .90 [59]. The scale also showed stability over a six-week interval, with reliability scores of .80. Convergent validity has been demonstrated with significant associations to seven other appraisal measures. Moreover, adequate concurrent, and divergent validity with other perceived support measures was demonstrated.

Personal Systems Thinking will be measured by Systems Thinking Survey (adapted for patients), a 20-item scale using a 5-point Likert response scale developed by [name]. The scale measures perceptions of personal system behaviors [61]. It has good reliability and construct and discriminate validity [62]. Test-retest was 0.74 and Cronbach’s Alpha was 0.89 [62]. The tool discriminated between those receiving high and low or no SystemCHANGE training (*p*=.05 and .01, respectively).

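### Exploratory mediator and moderator results choose the covariates for the hypothesis tests, with no bar on post-randomisation variables and in conflict with the primary analysis paragraph

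*Protocol article*

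**What the plan says.** All references are to the protocol article.

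- **Order and selection rule** (Statistical analysis, paragraph on descriptive and preliminary analyses). Before any hypothesis test, "exploratory analyses will be performed to examine the effect of various mediators and moderators on the relationship between intervention, adherence, and clinical outcome". Then: "The results of these analyses will determine what additional variables will be incorporated in the subsequent hypothesis testing (e.g., analysis of covariance"). No restriction to baseline variables is given.
- **Primary analysis** (same section, next paragraph). The groups are compared by Mann-Whitney, or by t-test if normality holds on the raw or transformed scale. Possible covariates from demographic data and screening-phase medication adherence (MA) are to be included.
- **Mediators and moderators.** Aims and Statistical analysis name social support and systems thinking as mediators, and ethnicity, perceived health and level of nonadherence as moderators. They have their own exploratory analysis, using Poisson regression and, for mediation, a Sobel test.
- **Timing** (Table 2). Under "Potential Mediators" the table lists social support, perceived health and personal systems thinking, ticked for Intervention and Maintenance but not for Screening. Randomisation follows screening (Design).
- **Role of perceived health** (Potential moderators and mediators). "Perceived health status, a potential moderator, will be measured by one question". Table 2 files it with the mediators.

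**The concern.** A covariate rule for a confirmatory comparison should be fixed in advance and should use only variables that treatment cannot have altered. The stated rule does neither.

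First, it admits mediators. A variable on the path from intervention to adherence absorbs part of the effect when it is adjusted for. The treatment coefficient then answers a different question from the primary aim, which asks whether the intervention improves MA overall.

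Second, covariates are chosen after seeing how they bear on the relation between intervention and adherence. The p-value of the later test then depends on an earlier look at the same contrast. This applies even to harmless baseline variables such as ethnicity.

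Third, the rule and the primary analysis paragraph cannot both be followed as written: one leaves the covariate list open, while the other names two pre-randomisation sources and tests that have no place for a covariate. Two analysts could reach different primary results from the same text.

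**Working it through.** **1. The plan's own sample size.** Inputs from Statistical analysis: "We use an alpha of .05 and provide for 90 % power to detect indicated effect sizes"; "An effect size difference of 70 % is based on a conservative estimate of our pilot work", read here as a standardised difference of 0.7; 46 per group. Two-sided testing is assumed because sidedness is not stated.

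- Normal approximation: n = 2(1.96 + 1.2816)² / 0.7² = 42.9, so 43 per group.
- Exact t-test: 43.87, so 44.
- Allowing for the Mann-Whitney relative efficiency of 0.955: 43.87 / 0.955 = 45.94, so 46. This matches the plan.
- Power of the t-test at 46 per group and d = 0.7: 0.913.

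The sample size is therefore not in dispute.

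**2. Effect of adjusting for a mediator.** Let the within-arm SD of outcome and mediator be 1. Let the intervention shift the mediator by a SD, and let a share m of the total effect d = 0.7 pass through it. Then:

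- outcome-on-mediator slope: b = m × d / a
- adjusted treatment coefficient: d × (1 − m)
- its standard error, approximately: √[(2/46) × (1 − b²) × (1 + a²/4)]

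The last factor reflects the correlation between mediator and treatment. The documents give neither m nor a, so both are assumptions: m from 25 to 75%, a from 0.7 to 0.9.

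Worked case, m = 50% and a = 0.7: b = 0.5; SE = √(0.04348 × 0.75 × 1.1225) = 0.191; 0.35 / 0.191 = 1.83; power about 0.44.

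| Share mediated | Adjusted estimate | Power at 46 per group (simulated, a = 0.9 to 0.7) |
|---|---|---|
| unadjusted | 0.70 | 0.91 |
| 25% | about 0.52 | 0.63 to 0.67 |
| 50% | 0.35 | 0.37 to 0.44 |
| 75% | about 0.17 to 0.18 | 0.15 to 0.22 |

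The formula agrees with the simulation to within about 0.01. Even if the variable mediates nothing (b = 0), the SE rises from √(2/46) = 0.209 to between 0.221 and 0.229, and power falls from 0.91 to about 0.88 to 0.86.

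**3. Data-driven covariate choice.** Under the null, with 46 per arm and 3 or 5 independent prognostic covariates (coefficient 0.3 each, assumed), taking the smallest treatment p-value over all covariate subsets rejects in about 9 to 14% of trials instead of 5%: about 10% with three covariates and 13 to 14% with five. This is a worst-case search, not a procedure that the protocol describes.

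**4. Perceived health.** Aims, Potential moderators and mediators, and the exploratory aims in Statistical analysis all make it a moderator. Table 2 makes it a mediator and shows no screening value. The moderator-testing text itself slips and introduces its list, perceived health included, as mediators. A moderator should be measured before allocation; Table 2 does not provide for that.

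**The case against.** The strongest reply is the primary analysis paragraph. It names only demographics and screening-phase MA, both pre-randomisation, and repeats the sentence for the secondary analysis. Mediators have their own exploratory analysis, and ANCOVA appears in the selection rule only as an example. On that view the rule is loose wording, not a plan to put mediators in the primary test. This has weight: it means that mediators may enter, not that they will. But the paragraph does not say that its covariates are the only ones, and it does not withdraw the rule for additional variables, so the conflict stands.

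Two stronger readings are tempting, and the text supports neither.

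- A reader might infer that the primary estimate will not be the total effect, or that the test will reject in 10% or more of null trials. The article commits to no particular added variable and describes no search for the smallest p-value. It also does not say whether group labels are masked during the exploration.
- A reader might infer that every value in the Table 2 mediator block has been altered by treatment. The columns are phases, not visits, and the intervention phase opens with a baseline home visit. A value taken there would follow randomisation but might precede any intervention content. Nor does the article say that the intervention is meant to change perceived health. Still, the selection rule is not limited to such early values.

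This is also not a detail properly left to an analysis plan: the article states a rule, and the rule is unsound as worded.

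**Conclusion.** The concern holds as a conflict between two stated covariate rules, one of which permits adjustment for variables measured after randomisation and selects covariates from the data. Following that rule could bias the primary estimate towards a direct effect and weaken the meaning of its p-value. The figures show what is at stake if a mediator entered (estimate about 0.52 to 0.17 instead of 0.70; power about 0.67 to 0.15 instead of 0.91). They rest on assumed mediated shares of 25 to 75%, an assumed mediator shift of 0.7 to 0.9 SD, and normal outcomes; they are not predictions for this trial. The 9 to 14% type I error is a worst-case figure.

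The perceived-health discrepancy is a separate and smaller inconsistency that affects only an exploratory analysis. Ethnicity and level of nonadherence are baseline variables, so adjusting for them removes no treatment effect; for these only the data-driven choice is at issue.

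**What to change.** 1. Delete the sentence that lets exploratory results choose variables for hypothesis testing, or restrict it explicitly to the exploratory aims.
2. Pre-specify one primary model that can use covariates, for example ANCOVA on raw, transformed or rank-transformed MA, with the scale fixed in advance. Adjust only for pre-randomisation variables: screening-phase MA (or its stratum) and any demographics named now. Listing covariates while keeping a plain Mann-Whitney or t-test would not resolve the conflict.
3. Run the mediator and moderator analyses separately, after the primary test.
4. In Table 2, list perceived health as a moderator, ask that single question before randomisation, and correct the moderator paragraph that calls these variables mediators.

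The cost is wording plus one question at an existing screening telephone contact; no extra participants are needed. Adjustment for centre is optional, since the randomisation section does not describe centre as a stratification factor. Baseline scores on the 23-item support scale and the 20-item systems-thinking scale would help the mediation analysis, but they add burden and are not needed for this correction. The change should be made before outcome data are examined by group.

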## Methods

### Aims

The primary aim of the trial is to determine whether the SystemCHANGE™ intervention is more effective than the attention control intervention in improving MA in adult kidney transplant recipients at the completion of the intervention and maintenance phases. We hypothesize adult kidney transplant recipients participating in the SystemCHANGE™ intervention will have higher immunosuppressive MA rates than those participating in the attention control at the completion of intervention and maintenance phases. A secondary aim is to examine the patterns of MA in this group. We will determine when the intervention becomes effective (e.g., what “dose” is needed) and what the pattern of decay in medication adherence is over time in both groups. Our exploratory aims are to determine whether the SystemCHANGE™ intervention is more effective than the attention control in decreasing poor health outcomes (e.g., infection, acute/chronic rejection, graft loss, death, and increasing creatinine/blood urea nitrogen,), to explore potential mediators (social support and systems-thinking) and moderators (ethnicity, perceive health and level of medication nonadherence) of MA, and to determine whether the SystemCHANGE™ intervention is cost-effective. We hypothesize patients in the SystemCHANGE™ intervention will demonstrate lower levels of poor outcomes than attention controls at 12 months. We also hypothesize the cost-effectiveness ratio for the SystemCHANGE™ intervention will be less than the cost-effective ratio for the attention-control intervention.

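### The primary hypothesis covers adherence at 6 and 12 months, but alpha, power and sample size are set for 6 months only, and the text does not say whether success needs both time points or either

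*Protocol article*

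**What the plan says.** In the protocol article, Aims states the primary aim as showing that SystemCHANGE is more effective than attention control "in improving MA in adult kidney transplant recipients at the completion of the intervention and maintenance phases". Statistical analysis repeats this: the primary analysis compares the groups "at the completion of the 6-month intervention and 6-month maintenance phases", and the hypothesis is that the intervention group "will have higher immunosuppressive MA rates than the attention-control group at the completion of intervention and maintenance phases". The comparison is a two-group Mann-Whitney test, or a t-test if normality holds. It is not a joint test over time, so two time points mean two tests.

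The sample-size paragraph in the same section has a narrower basis: "Sample size and power calculations are based on comparing expected change in medication adherence rate of patients in each group at six months". It then states: "We use an alpha of .05 and provide for 90 % power to detect indicated effect sizes in this two-arm randomized study". The effect size is given as follows: "An effect size difference of 70 % is based on a conservative estimate of our pilot work". The result is 46 per group, 92 in total. No effect is assumed for 12 months.

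The article names no leading time point, gives no order for the two tests, and does not say whether the hypothesis is met by one result or only by two.

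**The concern.** The hypothesis has two parts and the power basis has one. A colleague reading the power paragraph would take the trial to have 90% power for its primary hypothesis, but only the 6-month half was powered.

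The practical risk is a split result: significant at 6 months and not at 12, or the reverse. On the present text either could be called a success or a failure after the data are seen. The same section makes a further decision depend on the answer, since the cost analysis is dropped if there is no treatment effect. With two primary time points and no success rule, a split result leaves that condition undefined as well.

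**Working it through.** **Inputs from the article (Statistical analysis).** Alpha .05; power 90%; 46 per group, 1:1; 6-month comparison; Mann-Whitney by default.

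**Assumptions.**
- The stated 70% effect size is read as a standardized difference d = 0.70. With the 10-point mean difference this implies an SD of 10/0.70 = 14.3 points.
- Tests are two-sided. The article does not say so, but one-sided .05 would need only 35-36 per group.
- The article gives no correlation ρ between the 6- and 12-month test statistics. I use 0.5-0.9 as plausible, because the same patients and the same measure are used at both times, and show 0 as a bound.
- The article gives no 12-month effect. The values 0.50 and 0.35 below are illustrative only.
- All 46 per group are observed at both times.

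**Step 1. Reproduce the stated sample size.** Normal formula: n = 2(1.96 + 1.2816)²/0.70² = 42.9, so 43 per group. The t-test gives 44. Dividing by the Mann-Whitney efficiency 3/π gives 44 × π/3 = 46.1. The stated 46 is reproduced.

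**Step 2. Power at 6 months with 46 per group.** The test statistic has mean d√(n/2).
- Normal: 0.70 × √23 = 3.357; Φ(3.357 − 1.96) = 91.9%.
- t-test: 91.3%.
- Mann-Whitney: 0.70 × √(23 × 3/π) = 3.281; Φ(3.281 − 1.96) = 90.7%.

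So the 90% holds for the comparison it is stated for.

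**Step 3. Both required.** A false claim needs both tests to reject, so the error rate cannot exceed 5%. Joint power is P(Z₁ > 1.96 and Z₂ > 1.96) for a bivariate normal with the means of Step 2. Each pair below is Mann-Whitney, then normal.

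| ρ | d = 0.70 at both times | d = 0.70 then 0.50 |
|---|---|---|
| 0 | 82.2%, 84.4% | 58.9%, 61.5% |
| 0.5 | 84.3%, 86.2% | 62.3%, 64.6% |
| 0.7 | 85.6%, 87.4% | 63.7%, 65.9% |
| 0.9 | 87.7%, 89.2% | 64.8%, 66.9% |

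The 12-month test alone, Mann-Whitney then normal:
- d = 0.50: Φ(2.343 − 1.96) = 65%; Φ(2.398 − 1.96) = 67%.
- d = 0.35: Φ(1.640 − 1.96) = 37%; Φ(1.679 − 1.96) = 39%.

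**Step 4. Chance of a win at 6 months with no win at 12.** This is 6-month power minus joint power, for ρ from 0.5 to 0.9.
- Undiminished effect: from 91.9 − 89.2 = 2.7% to 90.7 − 84.3 = 6.4%.
- 12-month effect of 0.50: from 91.9 − 66.9 = 25.0% to 90.7 − 62.3 = 28.4%.

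**Step 5. Either counts, each tested at .05.** Family-wise error is 1 − P(|Z₁| < 1.96 and |Z₂| < 1.96). Independent tests give 1 − 0.95² = 9.75%. With ρ = 0.5, 0.7 and 0.9 it is 9.1%, 8.3% and 7.0%.

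**The case against.** This is a condensed article, and a test hierarchy is commonly left to the full protocol or SAP, so the absence of an alpha rule is not in itself a fault. That stands. What remains is the mismatch inside the text: a rule held elsewhere would not extend a 6-month power calculation to the 12-month half of the hypothesis.

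A reader might infer more than the documents support:

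- **That the error rate nearly doubles.** That fits only independent tests (9.75%), which is implausible here. It also needs the either-counts reading, whereas the hypothesis joins the two phases with *and*. Read as a conjunction, there is no inflation.
- **That each time point is tested at .05.** The article gives .05 once, in the power paragraph. Applying it to each test is an inference.
- **That the 90% power is wrong.** It is claimed for 6 months only, and there it holds.
- **That inflated error or lost power is unavoidable.** A fixed sequence starting at 6 months keeps 5% error and the 6-month power.
- **That the plan expects the effect to decay.** Design speaks of possible decay, and Statistical analysis examines decay in both groups. Falling adherence in both arms need not narrow the difference between them. The 12-month powers at 0.50 and 0.35 therefore rest on assumption alone.

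**Conclusion.** The point holds as an unresolved mismatch between a two-time-point primary hypothesis and a one-time-point power basis. It is not an error in the sample size: 46 per group gives about 91-92% power at 6 months.

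Under the more natural reading, with both required, the cost is in power. The shortfall from 90% is modest if the effect persists undiminished (84-89%) and grows if it shrinks. Under the either-counts reading the cost is an error rate of about 7-9%. These figures rest on d = 0.70, two-sided tests, the assumed correlations and complete data. The 12-month figures lean optimistic, because the randomization section replaces drop-outs from the intervention phase only, and any loss in the maintenance phase leaves fewer than 46 per group.

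It is worth correcting because the answer decides what a split result may claim, and the correction is cheap.

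**What to change.** Name 6-month adherence as the single primary endpoint, matching the sample size. Test 12-month adherence second, at .05, only if the 6-month result is significant. State that the 90% power applies to 6 months only, and give the 12-month power over a range of assumed effects, for example 0.70, 0.50 and 0.35, marked as assumptions.

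This keeps the overall error at 5% and the 6-month power at about 91-92% with no added patients. The chance of confirming both time points is the joint power in Step 3. The cost is a few sentences, and no confirmatory 12-month claim can be made if 6 months fails.

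If the investigators want the two time points to stand as co-equal, they should say whether both or either is needed and re-power accordingly. With an even split of alpha (.025 each), 46 per group gives 85-87% power per test, and restoring 90% per test needs about 51-55 per group.
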